### 3.1. Primary Outcome

#### Cancer-Specific Quality of Life (EORTC QLQ-C30 and QLQ-MY20)

The primary outcome of this study is HRQoL after the 3-month supervised exercise intervention compared with the waitlist control. HRQoL will be measured using the overall HRQoL summary score for the core HRQoL questionnaire of the European Organisation for Research and Treatment of Cancer Quality of Life Questionnaire (EORTC QLQ-C30, version 3.0) [46]. The EORTC QLQ-C30 is a widely used and well-validated cancer-specific instrument [3] with good psychometric properties in solid tumors [47,48]. It has acceptable reliability and validity in MM (Cronbach’s α = 0.70–0.92, except role function = 0.54), with an excellent ability to discriminate between patients in different objective disease states and a high responsiveness to changes in patients’ clinical status over time [3,49]. In a recent Delphi analysis, consensus was reached to collect patient-reported outcomes using the EORTC QLQ-C30 in patients with MM [50]. The minimal important difference (MID), defined as the smallest change in a HRQoL score considered important to patients that would lead the patient or clinician to consider a change in therapy, will be based on those estimated for individual scales of the QLQ-C30 in patients with MM [51].

The EORTC QLQ-C30 summary score encompasses all symptom (e.g., fatigue, pain) and function domains (e.g., emotional and social functioning) assessed by the QLQ-C30. The summary score is a strong prognostic factor for overall survival above and beyond that provided by clinical and sociodemographic variables for patients with MM [7]. The summary score also appears to have more prognostic value than the global QoL, physical functioning, or any other scale within the QLQ-C30 [7].

The European Organisation for Research and Treatment of Cancer Quality of Life Questionnaire Multiple Myeloma module (EORTC QLQ-MY20) is a reliable and valid instrument, recommended as a supplement to the QLQ-C30 instrument in patients with MM (Cronbach’s α = 0.70–0.92) [52]. As with the QLQ-C30, QLQ-MY20 domain scores are averaged and transformed linearly to a score ranging from 0–100. A high score for disease symptoms and side effects of treatment represents a high level of symptomatology or problems, whereas a high score for future perspective and body image represents better outcomes.

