## 5. Statistical Considerations and Data Analyses

A priori power calculations determined that a sample of 44 participants (*n* = 22 per group) will be needed to detect a mean difference of 6.7 points [51] between groups on the EORTC QLQ-C30 MY20 after the 3-month supervised exercise phase, with 80% power and 5% alpha. To account for an anticipated dropout rate of 25%, 60 participants will be recruited to the study. A difference of 6.7 on the physical function subscale of the EORTC QLQ-C30 MY20 questionnaire, determined by receiver operating characteristic curve analysis, corresponds to the minimum clinically meaningful change considered important by people with MM [51].

Data will be analyzed using the Stata statistical software package (version 15.0, StataCorp, College Station, TX, USA). Data entry will be performed in duplicate, and accuracy will be assessed with automatic cross-checking procedures. Range checks for data values will be performed to promote data quality. Data will be assessed for normality using the Shapiro–Wilk test. Subsequent analyses will include standard descriptive statistics, *t* tests, correlation, regression, and one-way repeated measures ANOVA or the comparable non-parametric test as necessary to examine differences among timepoints. Each model will include covariates, as appropriate, and will be adjusted using the baseline value as a fixed continuous covariate. For accelerometer data, means and 95% confidence intervals will be calculated and repeated measures accounted for across multiple days within participants. Quality of life questionnaire items will be analyzed using random effects mixed modelling with Fisher’s least significant difference tests for post hoc analyses to compare mean changes in outcomes between groups at each assessment period, with time and group as the fixed factors. A time × group interaction term will be used to formally test for differences between groups (alpha = 0.05).

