There are several limitations of the proposed study that warrant discussion. Our target population will be limited to those who are able to attend frequent testing and training visits and who are able to obtain an approval to participate from their treating physician. Arguably, those who are frailer, with limited mobility, and who may elicit a greater response from the intervention, will not be included in the study. Whilst the heterogeneous group of people with MM will demonstrate the ability of exercise to elicit improvements across the MM continuum, the study is not powered to conclude its effects within specific disease stages. Finally, the waitlist control group may increase their physical activity, despite being asked to maintain their activity levels for the first 12 weeks, reducing our ability to observe effects of the intervention.

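### The 6.7-point target behind the sample size is justified only for the QLQ-C30 physical function scale, so 80% power is not established for the primary outcome, the QLQ-C30 summary score

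*Protocol article*

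**What the plan says.** Section 3.1 fixes the endpoint and its timing: "The primary outcome of this study is HRQoL after the 3-month supervised exercise intervention compared with the waitlist control". It then fixes the score: "HRQoL will be measured using the overall HRQoL summary score for the core HRQoL questionnaire", that is, of the QLQ-C30. The same section explains that the summary score draws on all the symptom and function domains of the QLQ-C30. It sets that score apart from physical functioning when comparing their prognostic value. On the minimal important difference (MID), it says that the values used "will be based on those estimated for individual scales of the QLQ-C30 in patients with MM".

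Section 5 says that "a sample of 44 participants", 22 per group, is needed "to detect a mean difference of 6.7 points [51] between groups on the EORTC QLQ-C30 MY20" after the supervised phase, with 80% power and 5% alpha. Recruitment is set at 60 to allow for 25% dropout. The justification of the figure comes two sentences later. There it is tied to one scale, "A difference of 6.7 on the physical function subscale of the EORTC QLQ-C30 MY20 questionnaire", as the smallest change that matters to patients, from an ROC analysis in the same cited source.

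Section 5 also states that all tests are two-tailed and that models adjust for the baseline value. It gives no SD, standardised effect or baseline correlation.

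**The concern.** The target difference and the primary outcome refer to different scores. A minimal important change on one function scale is not automatically the minimal important change on a composite of all function and symptom domains, and the spread of the two scores need not be the same either. The article gives no target difference derived for the summary score.

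The instrument name adds to the uncertainty. Section 3.1 describes the QLQ-C30 and the QLQ-MY20 as two questionnaires, the second supplementing the first. The MY20 domains it lists (disease symptoms, side effects of treatment, future perspective, body image) contain no physical function scale. A reader of the sizing sentence alone cannot tell which score was powered.

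What is at stake is how a null primary result would be read. As written, Section 5 invites the reading that a non-significant result comes from a trial with 80% power for a difference that patients would notice. That reading needs support for the summary score itself, and the text does not supply it.

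**Working it through.** **Inputs from the article.** Difference Δ = 6.7 points; n = 22 per group; power 80%; alpha 0.05, two-tailed (Section 5); 1:1 allocation (Section 2.4); dropout 25% and 60 recruited (Section 5). No SD is given, so 44 cannot be reproduced forwards. It can only be solved backwards for the SD.

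**Dropout.** 44 / (1 − 0.25) = 58.7, rounded up to 59. The stated 60 is consistent: 60 × 0.75 = 45 evaluable.

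**Implied SD, two-sample t-test.** With d = Δ/SD, 42 degrees of freedom and noncentrality d × √(22/2), 80% power at two-sided 5% requires d = 0.8646. Then SD = 6.7 / 0.8646 = 7.75.

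**Implied SD, normal approximation.** d = (1.960 + 0.842) × √(2/22) = 0.845, so SD = 6.7 / 0.845 = 7.93. The two methods agree closely. As a forward check, SD 7.7 gives 22 per group by the t-test, with power 80.5%.

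**What this SD may be.** The planned analysis adjusts for baseline. If r is the correlation between baseline and week 12, the residual SD is approximately raw SD × √(1 − r²), ignoring the one degree of freedom spent on the covariate. So 7.75 could be a raw SD or a residual SD.

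**Illustration.** The raw SDs below are assumptions, not figures from the article. The difference is held at 6.7. The last column is r = √(1 − (7.75/SD)²).

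| Assumed raw SD | Power, 22 per arm, unadjusted | Power, 30 per arm, unadjusted | r needed for 80% with 22 per arm |
|---|---|---|---|
| 7.75 | 80% | – | 0 |
| 10 | 58% | 72% | 0.63 |
| 12 | 44% | 57% | 0.76 |
| 15 | about 30% | 40% | 0.86 |

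**What 44 evaluable participants deliver in SD units.** These figures need no assumption about the SD. At 80% power the detectable difference is:
- unadjusted: 0.86 SD
- r = 0.5: 0.8646 × √(1 − 0.25) = 0.75 SD
- r = 0.7: 0.8646 × √(1 − 0.49) = 0.62 SD

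**The case against.** The strongest defence is that the sizing sentence names no subscale. Section 3.1 says, directly under the primary outcome, that MIDs are taken from individual QLQ-C30 scales. On that reading the summary score was the score powered, with a target difference openly borrowed from one of its components. This stands in part. A reader might infer that the calculation was done for a different endpoint, but the text does not establish that. What it does establish is narrower: the only justification offered for 6.7 belongs to physical function, and nothing carries it over to the summary score.

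A second tempting inference is that an SD of 7.75 is too small, given that the Discussion refers to "the heterogeneous group of people with MM". The article does not support this. It reports no SD for any QLQ-C30 score, and the Discussion's remark concerns disease stage and the lack of power within stages, not the spread of scores. With baseline adjustment, 7.75 may also be a residual SD, which the table shows is compatible with a larger raw SD.

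Third, this is a journal article condensing a full protocol that is not shown, and an SD or correlation may stand there. That is fair, so the absence of an SD is not the point here. The point is the mismatch between two statements that the article does make.

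Fourth, running the two questionnaire names together is loose shorthand, since Section 3.1 and Table 1 pair them under the primary outcome. By itself that is editorial. It matters here because it hides which score the 6.7 points refer to.

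**Conclusion.** The point holds as a mismatch between the primary outcome in Section 3.1 and the justification of the target difference in Section 5. The stated 80% power for a clinically meaningful difference is not established for the QLQ-C30 summary score.

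No stated number is shown to be wrong: 22 per group is attainable for 6.7 points if the raw or residual SD is about 7.75, and the dropout step reproduces. The actual power for the primary test cannot be given, because the article contains neither an MID nor an SD for the summary score. The 58%, 44% and roughly 30% at raw SDs of 10, 12 and 15 show only how sensitive the claim is. They assume an unadjusted two-sample t-test and a target kept at 6.7.

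**What to change.** Keep N = 60 and rewrite the power paragraph in Section 5 for the QLQ-C30 summary score at 3 months. Either of these would do:

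- State the target difference and the SD for the summary score, with the baseline correlation if one is used, and give the source of each.
- State what 44 evaluable participants deliver: 80% power for 0.86 SD unadjusted, or about 0.75 to 0.62 SD with a baseline correlation of 0.5 to 0.7.

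Describe 6.7 points as the MID of the QLQ-C30 physical function scale, and name the QLQ-C30 and QLQ-MY20 separately. Do not claim 80% power for 6.7 points on the primary outcome unless both that difference and a residual SD of about 7.7 or less are justified for the summary score. The physical function scale need not become a new endpoint: neither Section 3.2 nor Table 1 lists it as a secondary outcome, and the rewrite does not require it.

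The cost is wording and one recalculation. No participants are added, and randomisation and the primary analysis are unchanged. The power statement may become less favourable.

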The number of participants who provide data at each timepoint will be reported, with reasons as to why participants did not attend. Incomplete data and missing values will primarily be managed using intention-to-treat analyses, using a 70% cut-point for adherence. To ensure the robustness of the findings, a secondary sensitivity analysis will be performed [109]. Non-continuous data will be analyzed using multinomial logistic regression. Metabolomics and lipidomics data will be evaluated using multivariate statistics, including principal component analysis and sparse partial least squares discriminant analysis. The blood molecular time-series measures will be analyzed to determine the metabolic and immune pathways altered by exercise and to determine biomarkers of responders for physical fitness, fatigue, and pain, if any. Exercise and control groups will be further stratified by therapy and remission duration. All tests will be two-tailed, and an alpha level of 0.05 will be applied as the criterion for statistical significance. There are no interim analyses planned or early trial termination guidelines.

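### For continuous secondary outcomes, a normality check followed by a switch to rank tests conflicts with the promised baseline adjustment and costs precision

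*Protocol article*

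**What the plan says.** Three consecutive sentences in section 5 (Statistical Considerations and Data Analyses) of the protocol article carry the point.

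1. "Data will be assessed for normality using the Shapiro–Wilk test". No significance level is given, and no rule on whether arms are tested separately or together.
2. The analyses that follow include t tests, correlation, regression and "one-way repeated measures ANOVA or the comparable non-parametric test as necessary to examine differences among timepoints".
3. "Each model will include covariates, as appropriate, and will be adjusted using the baseline value as a fixed continuous covariate".

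The same section gives several data types their own method:

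- "Quality of life questionnaire items will be analyzed using random effects mixed modelling", with a time-by-group interaction as the formal between-group test at the 5% level and no rank alternative.
- "Non-continuous data will be analyzed using multinomial logistic regression".
- Metabolomic and lipidomic data go to multivariate methods, and accelerometer data have their own repeated-measures handling.

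On the primary outcome, section 3.1 says "HRQoL will be measured using the overall HRQoL summary score for the core HRQoL questionnaire" (the EORTC QLQ-C30), which falls naturally under the quality-of-life mixed model.

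**The concern.** The normality check has no stated purpose other than to inform the choice in the sentence after it. That choice leads to tests which cannot do what the third sentence asks. The standard rank counterparts of the t test and of repeated measures ANOVA (rank-sum, signed-rank, Friedman) have no place for a continuous baseline covariate.

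This matters for the continuous outcomes with no method of their own: cardiorespiratory fitness, strength, DXA and pQCT measures, and the blood markers of section 3.2.10. For these, a preliminary p-value on the trial's own data could decide whether the result is a baseline-adjusted mean difference or an unadjusted rank comparison. Similar outcomes could then be reported on different scales. With about 22 evaluable participants per arm, the precision gained from baseline adjustment is worth keeping.

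**Working it through.** **The plan's own figures.** Section 5 gives 22 per group for a 6.7-point difference, 80% power and two-sided 5% alpha. No SD is stated, so it can only be solved for:

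- Normal approximation: SD = 6.7 / [(1.960 + 0.842) × √(2/22)] = 6.7 / 0.845 ≈ 7.93.
- Exact noncentral t: SD ≈ 7.75, a standardised effect of 6.7 / 7.75 ≈ 0.865.
- Dropout: 44 / (1 − 0.25) = 58.7, so 59; the stated 60 agrees.

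The value 0.865 is used below only as a reference effect. It comes from the primary outcome's calculation; the article states no power for secondary outcomes.

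**Why adjustment matters.** If baseline and follow-up correlate at r, ANCOVA multiplies the residual variance by (1 − r²). The effective standardised effect becomes 0.865 / √(1 − r²): 0.91 at r = 0.3, 1.00 at r = 0.5 and 1.21 at r = 0.7. An unadjusted test stays at 0.865.

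**Simulation.** The set-up was 22 per arm, one follow-up visit and 3,000 simulated trials per scenario. Under the two-stage rule, Shapiro–Wilk at 0.05 in either arm sends the outcome to an unadjusted Mann–Whitney test; otherwise ANCOVA is used. The level, the per-arm testing, the correlations and the distributions (normal; capped at +0.8 SD; log-normal with log-SD 0.5) are assumptions. In the last two, the effect is added before capping or exponentiating.

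| Distribution | r | ANCOVA power | Rank test power | Loss (points) | Two-stage power |
|---|---|---|---|---|---|
| Normal | 0.3 | 84.4% | 78.8% | 5.6 | 84.1% |
| Normal | 0.5 | 89.2% | 77.7% | 11.5 | 88.0% |
| Normal | 0.7 | 97.4% | 76.3% | 21.1 | 95.3% |
| Capped | 0.3 | 74.0% | 73.4% | 0.6 | 73.4% |
| Capped | 0.5 | 80.2% | 72.9% | 7.3 | 72.9% |
| Capped | 0.7 | 91.9% | 75.2% | 16.7 | 75.2% |
| Log-normal | 0.3 | 76.6% | 77.0% | −0.4 | 77.6% |
| Log-normal | 0.5 | 83.7% | 77.9% | 5.8 | 79.9% |
| Log-normal | 0.7 | 94.3% | 78.0% | 16.3 | 81.4% |

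The loss from an unadjusted rank test is thus about 0–6 points at r = 0.3, 6–12 at 0.5 and 16–21 at 0.7.

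**How often the check fires.** At least one arm is flagged in 9–11% of truly normal outcomes (theory: 1 − 0.95² = 9.75%), in 80–82% of log-normal ones and in 86–100% of capped ones.

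**Type I error.** Across the nine null scenarios the two-stage rule rejects in 4.6–5.7%. The Monte Carlo standard error is √(0.05 × 0.95 / 3000) ≈ 0.4 points, so this is consistent with 5%.

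**What a log transform recovers.** The log of the log-normal scenario is exactly the normal scenario. ANCOVA on the log scale would therefore have the normal rows' power, about 84%, 89% and 97%.

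**The case against.** Several points on the other side are sound.

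- **Scope.** A reader might infer that the check governs every outcome, including the primary one. The text does not support that: quality-of-life items, non-continuous data, omics and accelerometer data each have their own stated method.
- **Wording of the switch.** The rank alternative is worded for differences over time, and nothing states that a Shapiro–Wilk p-value alone triggers it. The link is an inference, though a natural one. However, the list also contains t tests, and the time-by-group sentence directly follows the quality-of-life sentence. No other between-group method is clearly named for fitness, strength, scans or blood markers.
- **Rank methods can be extended.** Rank tests can be run on change from baseline, rank ANCOVA exists, and Hodges–Lehmann estimates give intervals. The article excludes none of these, so it would be too strong to say that estimates and intervals are necessarily lost. It names none of them either, and the ordinary counterparts do not adjust.
- **Detail left to the analysis plan.** Whether raw values or residuals are checked may properly be left to a statistical analysis plan that is not shown. That omission is not the point here. The point is that the article commits to a switch which its next sentence cannot accommodate.

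Two larger figures are tempting but unsupported. One is a fall in power from 80% to 68%, 61% or 52% at r = 0.5, 0.6 or 0.7. That assumes the 22 per group was calculated for a baseline-adjusted analysis, and that the outcome concerned can be switched; the article says neither. The other is a 34% chance (1 − 0.95⁸) that a normal outcome fails somewhere across two arms and four visits. That treats repeated visits of the same people as independent tests, and it counts 6- and 12-month visits although the waitlist is an untreated comparator for the first 12 weeks only.

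**Conclusion.** The concern holds for continuous secondary outcomes outside the quality-of-life mixed model. The text makes their method depend on the data and leads to tests that do not meet its own baseline-adjustment requirement.

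The size depends on the outcome. If baseline and follow-up correlate weakly, little is lost. At a correlation of 0.7 an outcome sent to an unadjusted rank test loses 16–21 points of power. For outcomes that really are normal the two-stage rule costs at most about 2 points (95.3% against 97.4% at r = 0.7), because it seldom fires. For skewed or bounded outcomes it fires most of the time; blood markers are plausible candidates, though the article gives no distributions.

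A reader might also infer that false positives increase; the simulations do not show this. The harm is lost precision, results on mixed scales and room for discretion. The primary analysis is not at issue. All power figures rest on the assumed effect of 0.865 and on the assumed correlations, distributions and trigger rule.

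**What to change.** In section 5, or in the analysis plan before any outcome data are seen:

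- Remove the normality test as the trigger for choosing a method.
- Name one baseline-adjusted mixed model, or ANCOVA at 3 months, as the between-group analysis for all continuous secondary outcomes.
- Check model residuals, by plots, rather than testing raw data.
- Pre-specify a log transform for skewed blood markers, and robust or bootstrap standard errors for other outcomes whose residuals look poor.
- Keep rank-based tests as sensitivity analyses.

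The cost is a change of wording and slightly more analysis work. Log-transformed markers would be reported as ratios rather than differences. Design and sample size do not change.

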### 2.4. Randomization

Following completion of the baseline testing session, participants will be stratified by disease stage (active treatment, transplant eligible; active treatment, transplant non-eligible; non-active; relapsed) before being randomly assigned (1:1 allocation ratio) to waitlist control (WT) or exercise intervention (EX) group. A research officer independent of the study will perform the randomization using a computerized random number generator. To ensure allocation concealment, a block size of four will be used. Randomization history will be kept secure by the independent research officer in an electronic password-protected file. The allocation result will be communicated in confidence by the independent research officer to the trial’s accredited exercise physiologist (AEP) within 48 h after completing the baseline testing session. The principal investigator will conduct all testing sessions and analyses and be blinded to group allocation. Un-blinding will not be permissible under any circumstances. Due to the nature of the study, neither the AEPs prescribing the training nor participants can be blinded to the randomization assignment.

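### Disease stage, the randomisation stratum, is not named in any model, and a block size of four is wrongly given as the means of allocation concealment

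*Protocol article*

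**What the plan says.** Protocol article, section 2.4 (Randomization): after baseline testing, "participants will be stratified by disease stage". There are four levels: active treatment and eligible for transplant, active treatment and not eligible, non-active, and relapsed. Allocation is 1:1. On concealment it says: "To ensure allocation concealment, a block size of four will be used". The same section adds two further measures: "A research officer independent of the study will perform the randomization using a computerized random number generator", and "Randomization history will be kept secure by the independent research officer in an electronic password-protected file". The principal investigator, who tests and analyses, is blinded. The trial exercise physiologist is told each allocation.

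Protocol article, section 5 (Statistical Considerations and Data Analyses): "Each model will include covariates, as appropriate, and will be adjusted using the baseline value as a fixed continuous covariate". For quality-of-life outcomes the mixed model has time and group as fixed factors, with their interaction as the formal test. Disease stage is not named as a term in any model. Later in the section, after the text on metabolomics, lipidomics and blood time series, comes: "Exercise and control groups will be further stratified by therapy and remission duration".

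**The concern.** There are two separate issues.

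First, stratified blocks force the arms to be balanced within each disease stage. The real variability of the treatment difference then no longer contains the between-stage component. A model without stage still counts that component in its residual, so its standard error is too large and its test conservative. The article itself suggests that stage matters for this outcome: section 3.1 says the questionnaire discriminates well between disease states, and section 7 expects symptoms to be most pronounced in relapsed disease. With 44 evaluable participants planned, precision that the design has already secured should not be left to discretion.

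Second, the reason given for the block size is wrong. Blocking balances group numbers. It conceals nothing, and a small fixed block within strata makes the next allocation easier to infer for anyone who knows the block size and what came before.

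**Working it through.** **The plan's own figure.** Section 5 gives 22 per group for a 6.7-point difference, 80% power and two-sided 5% alpha, then 60 recruited for 25% dropout.
- Dropout: 22 / 0.75 = 29.3, so 30 per group and 60 in total. This reproduces.
- The 22 per group cannot be checked independently, because no SD is stated. Solving backwards with the normal approximation: SD = 6.7 / [(1.960 + 0.842) × √(2/22)] = 7.93. With the t test it is 7.75, so d = 6.7 / 7.75 = 0.865. This d is inferred, not quoted, and is used below.

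**Precision.** Let R² be the share of variance left after baseline adjustment that disease stage explains. The article gives no value, so 0 to 0.20 is an assumption.
- Model standard error without stage relative to with it: 1/√(1 − R²). This is 1.00 at R² = 0, 1.05 at 0.10 and 1.12 at 0.20.
- Power with stage in the model (normal approximation, SD scaled by √(1 − R²)): 80%, 84% and 88%.
- Setting these against a flat 80% would overstate the gain, because stratified blocking already reduces the true variance of the unadjusted difference. A simulation allows for this: N = 44, four equally likely strata, blocks of four, 6,000 runs per setting, and an outcome taken as already adjusted for baseline.

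| R² | Type I error, without / with stage | Power, without / with stage | Gain (points) |
|---|---|---|---|
| 0 | 5.2% / 5.1% | 80.0% / 79.6% | −0.4 |
| 0.10 | 4.0% / 4.9% | 80.7% / 83.8% | 3.1 |
| 0.20 | 2.7% / 5.2% | 82.1% / 87.6% | 5.5 |

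The simulation standard error is about 0.3 points for type I error, √(0.05 × 0.95 / 6000), and about 0.5 points for power, √(0.8 × 0.2 / 6000). The figures at R² = 0 therefore show no difference. The cost of the term is three residual degrees of freedom: 44 − 2 = 42 without stage, 44 − 5 = 39 with it.

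**Predictability.** A 1:1 block of four has six possible orders. Take someone who knows the stratum, the block size and every earlier allocation in that stratum.

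| Position in block | Probability that the allocation is certain | Probability that the best guess is right |
|---|---|---|
| 1 | 0 | 1/2 |
| 2 | 0 | 2/3 |
| 3 | 1/3 | 1/3 × 1 + 2/3 × 1/2 = 2/3 |
| 4 | 1 | 1 |
| Average | (1/3 + 1)/4 = 33.3% | (1/2 + 2/3 + 2/3 + 1)/4 = 70.8% |

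Simple randomisation would give 0% and 50%. If all 60 participants fell in complete blocks, 60/3 = 20 allocations would be certain. With 15 per stratum (three full blocks and three further participants) the expected number is 4 × (3 × 1.333 + 0.333) = 17.3.

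**The case against.** The strongest reply is that the model point rests on silence. Section 5 allows further covariates where appropriate in every model, and the covariate list may be settled in an analysis plan that is not shown. Listing time and group describes the repeated-measures structure and need not exclude other terms: the baseline value is missing from that phrase too, yet the preceding general sentence requires it. This stands. A reader might infer that the models leave the stratum out, but the text supports only that it is not named.

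A reader might also infer that therapy and remission duration replace disease stage in the primary analysis. The sentence does not say so. It follows the blood-marker text and speaks of further stratification.

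On predictability, a reader might infer that the exercise physiologist can foresee allocations and influence who is enrolled next. The documents do not support this. Randomisation follows baseline testing, an independent officer performs it and holds the history, the tester is blinded in a trial described as single blind, and section 2.3 (Recruitment) gives the exercise physiologist no recruiting role. The 33% and 71% figures describe what a fully informed observer could infer, not what happens in this trial.

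Baseline adjustment may also absorb much of what stage explains, and then little or nothing is gained.

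What remains is that the stratum goes unnamed where the model's factors are listed, and that the reason given for concealment is wrong as written. An analysis plan could settle the first; it would not correct the second.

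**Conclusion.** The point holds as a clarification of the model and a correction of the randomisation text. If disease stage were omitted, the primary test would be conservative, with simulated type I error of 5.2% falling to 2.7% as R² goes from 0 to 0.20. Including it would gain about 0 to 5.5 points of power. Those figures rest on an assumed R², a back-solved effect size of 0.865 and equally likely strata. They do not show that the trial is invalid, that false positives are inflated, or that the stated sample size is wrong.

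The concealment statement is an error of reasoning. The real safeguards stand in the same section, and the fixed block of four weakens them only for someone who knows both the block size and the earlier allocations in a stratum.

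**What to change.** 1. Name the four-level disease-stage stratum as a fixed effect in the primary model and the other between-group models. Add a rule, set before outcomes are seen by group, for pooling very sparse strata. Cost: up to three degrees of freedom.
2. In section 2.4, attribute concealment to the independent officer, who generates and holds the allocations, and describe blocking as a means of balance. Cost: one sentence.
3. For anyone still to be randomised, use randomly varying block sizes that are not disclosed to trial staff. Cost: one setting in the randomisation program, and slightly more possible imbalance within strata. If randomisation is complete, only the first two changes apply.
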